### Statistical analyses

The primary outcome, serum IL-8 levels, is continuously scaled, so the target differences can be specified as a ‘standardised differences’ (0.2=small, 0.5=moderate, 0.8=large). On the assumption that there will be a moderate correlation of 0.7 between preintervention and postintervention measures and between repeated postintervention measures, as observed in previous work,^46^ and on the basis that there will be one baseline and five postoperative measures, we estimate that a sample size of 150 patients will allow us to detect a small-to-moderate target difference between groups of 0.4, with 90% power and 5% significance (two-tailed). We propose to recruit 170 patients (85 per group) assuming an attrition rate of between 10% and 15% for incomplete sampling, patient death and withdrawal.

This sample size is not expected to detect significant differences in important clinical outcomes. In a previous trial that recruited patients at increased risk of transfusion we observed the composite end point of any sepsis, inflammatory organ injury or death in 55% of patients.^36^ If this is replicated in the REDWASH trial, our sample size will allow us to detect a 40% difference in with 80% power and 5% significance. To detect a more modest reduction in this composite end point (20%) would require at least 324 patients per group. Specific morbidities and other adverse events are too infrequent for the trial to be able to detect differences between groups. Frequencies of these adverse outcomes will be tabulated, in line with guidelines for reporting adverse events in trials.^45^

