**Methods and analysis:**

Adult (≥16 years) cardiac surgery patients identified at being at increased risk for receiving large volume red cell transfusions at 1 of 3 UK cardiac centres will be randomly allocated in a 1:1 ratio to either red cell washing or standard care. The primary outcome is serum interleukin-8 measured at 5 postsurgery time points up to 96 h. Secondary outcomes will include measures of inflammation, organ injury and volumes of blood transfused and cost-effectiveness. Allocation concealment, internet-based randomisation stratified by operation type and recruiting centre, and blinding of outcome assessors will reduce the risk of bias. The trial will test the superiority of red cell washing versus standard care. A sample size of 170 patients was chosen in order to detect a small-to-moderate target difference, with 80% power and 5% significance (2-tailed).

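### Power for the primary outcome is given as 80% in the abstract and 90% in the statistical section, and the 90% at 0.4 SD with 150 patients does not follow from the stated inputs

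*Protocol article*

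**What the plan says.** The protocol article states the power for the primary outcome, serum IL-8, twice.

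- Abstract, Methods and analysis: the 170 patients were "chosen in order to detect a small-to-moderate target difference, with 80% power and 5% significance (2-tailed").
- Statistical analyses: "a sample size of 150 patients will allow us to detect a small-to-moderate target difference between groups of 0.4, with 90% power", again at the two-sided 5% level.

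The inputs are in Statistical analyses: a "moderate correlation of 0.7 between preintervention and postintervention measures and between repeated postintervention measures", one baseline and five postoperative measurements, and a target expressed as a standardised difference. The 150 is then raised to 170 (85 per group), "assuming an attrition rate of between 10% and 15% for incomplete sampling, patient death and withdrawal". The Primary outcome section says that IL-8 is adjusted for the preoperative value, and Plan of analysis specifies analysis of variance or regression with baseline adjustment. Allocation is 1:1.

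**The concern.** The outcome, the verbal description of the target, the significance level and the sidedness are the same in both places, but the power is 80% in one and 90% in the other. Two possible explanations fail.

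- **Attrition.** The 150 is already the number expected to remain out of 170, and recruiting more patients cannot lower power.
- **The clinical composite.** Statistical analyses uses 80% power for the composite endpoint. The abstract, however, attaches its 80% to the small-to-moderate difference, and the statistical section says the sample is not expected to detect differences in clinical outcomes.

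The statistical section also gives enough inputs to check the 90%, and the check fails. This is the justification of sample size for the primary outcome, so readers and the monitoring committee should be able to see which difference the trial was sized to detect, and with what power.

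**Working it through.** **Inputs.** d = 0.4 SD, 75 per group, two-sided 5%, r = 5 postoperative measures, one baseline and rho = 0.7 throughout (all from Statistical analyses); 1:1 allocation (Randomisation and code breaking); baseline adjustment (Primary outcome; Plan of analysis).

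**Assumptions added here.** The article names no formula. I take equal correlation between all pairs of measurements, the plain mean of the five postoperative values as the quantity compared, and 0.4 as a multiple of the SD of a single measurement.

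**Variance factor V**, relative to a single measurement:

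- Baseline-adjusted mean of five: (1 + 4×0.7)/5 − 0.7² = 0.76 − 0.49 = 0.27
- Change from baseline, mean of five: 0.76 + 1 − 2×0.7 = 0.36
- Mean of five, baseline ignored: (1 + 4×0.7)/5 = 0.76

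**Formulas.** n per group = 2(z₀.₉₇₅ + z_power)² V/d². Power = Φ(d/√(2V/n) − 1.96).

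**Trying to reproduce 150 at 90% power.** Here 2(1.960 + 1.282)²/0.16 = 131.3, so n per group is 131.3 × V:

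- V = 0.27: 35.5, so 36 per group, 72 in total
- V = 0.36: 47.3, so 48 per group, 96 in total
- V = 0.76: 99.8, so 100 per group, 200 in total

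None is 150.

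**Trying 80% power.** Here 2(1.960 + 0.842)²/0.16 = 98.1. With V = 0.76 this gives 74.6, so 75 per group and 150 in total. With V = 0.27 it gives 26.5, so 54 in total.

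**Power with 75 per group at 0.4 SD:**

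| Calculation | V | Power | Total for 90% |
|---|---|---|---|
| Baseline-adjusted, mean of five (as planned) | 0.27 | 99.7% | 72 |
| Change score, mean of five | 0.36 | 98.3% | 96 |
| Mean of five, baseline ignored | 0.76 | 80.2% | 200 |
| Baseline-adjusted, one postoperative value | 0.51 | 92.9% | 134 |
| Change score, one postoperative value | 0.60 | 88.5% | 158 |
| One postoperative value, unadjusted | 1.00 | 68.8% | 264 |

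For the planned row: √(2×0.27/75) = 0.0849; 0.4/0.0849 = 4.71; Φ(4.71 − 1.96) = 0.997. Noncentral t results differ by at most 0.6 points.

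**Could another common correlation rescue the 90%?** Power of 90% with 75 per group needs V = 0.16×75/(2×3.2415²) = 0.571. The baseline-adjusted factor (1 + 4rho)/5 − rho² is largest at rho = 0.4, where it is 0.52 − 0.16 = 0.36. Under the planned analysis with one common correlation, power at 0.4 SD is therefore never below 98.3%.

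**Difference detectable with 150 patients at 90% power:** 3.2415 × 0.0849 = 0.275 SD with baseline adjustment. With the baseline ignored it is 3.2415 × √(2×0.76/75) = 0.46 SD.

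**Attrition step.** 150/0.90 = 167, 150/0.85 = 177, and 1 − 150/170 = 11.8%. The 170 lies inside the stated range.

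**The case against.** **The planned analysis has more power than claimed.** On the stated inputs, 150 patients detect 0.4 SD with well over 90% power, so the statement could be called conservative. This stands as far as adequacy goes. A reader might infer from the mismatch that the trial is underpowered, for instance because 200 patients would be needed for 90%. That figure applies only if the baseline is discarded, and the article plans to adjust for it and lists the pre-post correlation among its inputs.

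**The formula is not given, and an article may leave it to the full protocol.** This is fair, and its absence is not criticised here. The 99.7% depends on the assumptions listed above. For one postoperative value adjusted for baseline, 150 patients give 92.9% and 134 suffice for 90%. That reading makes 150 enough, but it leaves out the five measures that the section names as a basis of the calculation, and it still does not return 150 at 90%. The nearest figure in the table, 88.5% for a single-value change score, has the same defect and would need 158.

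**The abstract's 80% may simply be the correct one.** It matches the calculation that ignores the baseline exactly. But that match is not unique: one baseline-adjusted value tested at 1% (5% divided over five time points) also needs 150 for 80% power. The article mentions no such division. The route to 150 therefore remains an inference.

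**The attrition allowance.** A reader might object that 170 less 15% leaves only 144 to 145. The article gives a range of 10% to 15%, and 170 corresponds to 11.8%, so that step is consistent and is no fault.

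**A null result is read from its confidence interval.** This is true, and the article commits to 95% intervals. It lowers the practical stakes but does not make the stated power correct.

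**Conclusion.** The point holds as a reporting error in a figure that readers rely on. The contradiction between 80% and 90% needs no formula to see. Separately, 90% power at 0.4 SD with 150 patients does not follow from the stated inputs. With equal correlations of 0.7 and the mean of five postoperative values, the planned analysis gives about 99.7%; leaving the baseline out gives about 80%.

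The documents do not support the conclusion that too few patients are planned. Nor do they establish which calculation the sponsor ran, although the agreement of the abstract's 80% with the 150 makes one that ignores the baseline plausible.

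**What to change.** Keep 170 patients. Remove the claim of 90% power at 0.4 SD, and put one reconciled statement in both the abstract and Statistical analyses, saying whether baseline adjustment is credited. Either of these agrees with the stated inputs:

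- 150 evaluable patients give about 90% power for 0.275 SD, with baseline adjustment and correlations of 0.7; or
- 150 evaluable patients give at least 80% power for 0.4 SD on the mean of five postoperative values, conservatively taking no credit for baseline adjustment.

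The sponsor knows which calculation was made and should choose accordingly. If the second is used, the text should make clear that the pre-post correlation does not enter the figure. The attrition sentence can stay as it is. The cost is wording only: no change to patient numbers, analysis or error rate, though a headline power of 80% would look less favourable than 90%.

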#### Plan of analysis

The primary analysis will take place when follow-up is complete for all patients and will be performed on an intention-to-treat basis. Means for continuous outcomes (transformed logarithmically if required) will be compared using analysis of variance or regression modelling, adjusting for baseline values where available. Findings will be reported as effect sizes with 95% CIs. Time to classification as fit for discharge, ICU and postoperative hospital stay will be analysed as time-to-event data using regression modelling for survival data. Frequencies of adverse clinical outcomes will be tabulated, in line with guidelines for reporting adverse events in trials.^45^ A mechanism substudy will consider links between markers of inflammation, cellular and platelet activation, and organ injury, in the first 60 participants from Glenfield Hospital (approximately 30 for each group).

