### Study population and recruitment

The study will be carried out at three tertiary cardiac surgery centres in the UK: the University Hospitals of Leicester National Health Service (NHS) Trust, the Royal Victoria Hospital, Blackpool and University Hospitals Coventry and Warwickshire NHS Trust. These units perform over 3500 major cardiac procedures per year, of whom over 875 will be at risk of LVBT (from the UK National Audit of Blood Transfusion in Cardiac Surgery^11^). If red cell washing is effective, its clinical benefits and impact on resource use will be most apparent in patients at greatest risk of LVBTs. Patients at risk of LVBT will therefore be identified preoperatively using a risk score developed and validated by these investigators in a multicentre population.^17^

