### Primary and secondary end points

#### Primary outcome

The primary outcome is serum IL-8 levels measured from venous blood samples taken at five postoperative time points; on return to intensive therapy unit (ITU), and 6, 24, 48 and 96 h, adjusted for baseline (preoperative) values. IL-8 levels reflect the severity of the systemic inflammatory response and are an important predictor of adverse clinical events in cardiac surgery patients.^33^
^34^ Our previous research^35^ has indicated that blood transfusion is associated with increases in the levels of this proinflammatory cytokine that are maximal between 4 and 24 h postoperatively (figure 2). However, the intervention period in the REDWASH trial extends to 48 h postsurgery and therefore IL-8 levels will be measured up to 96 h to capture events after this point.

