#### Randomisation and code breaking

Patients will be randomly assigned in a 1:1 ratio using an internet-based randomisation system (Sealed Envelope Ltd, MHRA recognised facility). Randomisation will be stratified by: (1) study site; (2) type of procedure, coronary artery bypass grafts (CABG), valve, CABG and valve, other. Random allocations will be generated only after the relevant baseline data to identify the patient and the surgeon have been entered into the system, guaranteeing concealment of allocation and a definitive log of participants. Patients who consent will be randomised by a member of the research team at a participating site. If patients are unexpectedly rescheduled, they will retain their study numbers and randomised allocation.

Detailed instructions for the randomisation process will be provided in a separate manual (figure 3).

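### Randomisation is stratified by site and procedure type, but the stated analysis adjusts for baseline only; if those factors predict IL-8, the intervals will be too wide and the test conservative

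*Protocol article*

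**What the plan says.** The section on randomisation and code breaking defines the strata: "Randomisation will be stratified by: (1) study site; (2) type of procedure, coronary artery bypass grafts (CABG), valve, CABG and valve, other". There are three sites; the section on study population and recruitment says "The study will be carried out at three tertiary cardiac surgery centres in the UK". The abstract lists this stratification among the features meant to reduce the risk of bias.

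Two places describe the adjustment. The Plan of analysis, for all continuous outcomes, reads: "Means for continuous outcomes (transformed logarithmically if required) will be compared using analysis of variance or regression modelling, adjusting for baseline values where available". The Primary outcome section gives the IL-8 measurement times and their adjustment: "on return to intensive therapy unit (ITU), and 6, 24, 48 and 96 h, adjusted for baseline (preoperative) values".

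No section puts site or procedure type into an analysis model, and none says that they will be left out.

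**The concern.** Stratified allocation removes most of the chance imbalance between arms in site and procedure type, so the treatment difference varies less from trial to trial than under simple randomisation. An analysis gets the benefit only if its model contains those factors. If it does not, the variance they explain stays in the residual term, and the reported standard error describes a less precise trial than the one that was run.

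What is at stake is mainly precision. The Aims and objectives ask for estimated mean differences, and the Plan of analysis promises effect sizes with 95% CIs. Interval width is therefore a main product of this trial, and the article's wording, followed literally, would overstate it whenever site or procedure predicts IL-8.

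**Working it through.** **Inputs from the protocol.** Site has 3 levels and procedure type 4, so there are 3 × 4 = 12 strata, and main effects need (3 − 1) + (4 − 1) = 5 degrees of freedom. The Statistical analyses section gives 150 evaluable patients (75 per arm), a standardised difference of 0.4, two-sided 5% significance and 90% power. It assumes a "moderate correlation of 0.7 between preintervention and postintervention measures and between repeated postintervention measures" and that "there will be one baseline and five postoperative measures".

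**Input not in the protocol.** R² is the share of residual IL-8 variance explained by site and procedure type. It is taken as 0% to 30%, as an assumption.

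**The protocol's own figure.** This is needed only to choose a base for the power comparison. With ρ = 0.7 and the mean of r = 5 postoperative values, the variance factors are:

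- Without baseline: (1 + 4 × 0.7)/5 = 0.76.
- Adjusted for baseline: 0.76 − 0.7² = 0.27.

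The number per arm is 2f(z₁ + z₂)²/0.4².

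- Adjusted, 90% power: 2 × 0.27 × (1.960 + 1.282)²/0.16 = 35.5, so 36 per arm and 72 in total. The stated 150 is not reproduced.
- Unadjusted, 80% power (the abstract's figure): 2 × 0.76 × (1.960 + 0.842)²/0.16 = 74.6, so 75 per arm and 150 in total.

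Both variances are carried forward. How the 150 was derived is a separate matter.

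**Effect of omitting the strata.** With balanced strata, the true SE is √(2f(1 − R²)/75), while the model that omits them reports √(2f/75). It follows that:

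- CI width ratio = 1/√(1 − R²), whatever f is.
- True type I error = 2[1 − Φ(1.96/√(1 − R²))].
- Power, strata omitted = Φ((0.4 − 1.96 × reported SE)/true SE).
- Power, strata included = Φ(0.4/true SE − 1.96).

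| R² (assumed) | CI width ratio | True type I error | Power omitted / included, f = 0.76 | Power omitted / included, f = 0.27 |
|---|---|---|---|---|
| 0% | 1.000 | 5.0% | 80.2% / 80.2% | 99.71% / 99.71% |
| 10% | 1.054 | 3.9% | 81.5% / 84.2% | 99.82% / 99.87% |
| 20% | 1.118 | 2.8% | 82.9% / 88.1% | 99.90% / 99.95% |
| 30% | 1.195 | 1.9% | 84.5% / 91.9% | 99.95% / 99.99% |

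**Check by simulation.** The set-up was 150 patients, 12 strata, blocks of 4 (assumed) and additive site and procedure effects. The CI width ratios were 1.05, 1.12 and 1.20 for R² of 10%, 20% and 30%. Type I error with the strata omitted was about 3.5–3.9%, 3.2% and 2.2%; with them included it stayed between 4.5% and 5.3%. At R² = 0 the intervals with the strata included were 0.1–0.2% wider, which is all that the five degrees of freedom cost.

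**The case against.** The strongest reply is that this is a condensed article. The Plan of analysis sentence is generic, it never says that baseline is the sole covariate, and adding site and procedure type is compatible with regression modelling. A full protocol or SAP may already include them. It stands that silence is not a decision to exclude, and that the two sections do not formally contradict each other. But the article does more than stay silent: in two places it says what the analysis adjusts for, and the design factors are in neither. An analyst following those statements would leave them out.

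The second reply is that the error is on the safe side and its size is unknown. Both parts stand. The estimate is not biased, false positives fall rather than rise, and R² is assumed. The range from 8% to 45% in large volume transfusion between units, given in the Introduction, does not supply it. That is audit incidence across UK units, not IL-8 variance at three sites in a population selected by risk score.

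A reader might also draw stronger conclusions from the same sentence, and the documents do not support them:

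- **The IL-8 scale will be chosen after seeing the data.** The text leaves the log transformation conditional but does not say when or by what rule it is decided. An article commonly leaves that to the full protocol or SAP.
- **Analysis of variance or regression is an open choice of method.** With the same terms, the two give the same comparison.
- **Five time points mean five tests and an inflated error rate.** No section proposes this. There is one primary outcome, and the sample size treats it as one group difference.
- **The trial loses material power.** Under the baseline-adjusted model with correlation 0.7, power exceeds 99% either way.

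**Conclusion.** The point holds in a limited form. The stated adjustment set leaves out both stratification factors. If these predict IL-8, the model-based 95% CIs are too wide and the test is conservative; the estimate itself is sound. The excess width is about 5%, 12% or 20%, and the true type I error about 3.9%, 2.8% or 1.9%, if the strata explain 10%, 20% or 30% of the residual variance. With no prognostic effect nothing is lost.

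These figures rest on the assumed R² and on near-balance within strata. The loss of power is about 3, 5 or 7 points on the variance that ignores baseline, and negligible on the baseline-adjusted variance that the protocol's assumptions imply. The case for change therefore rests on interval width and a correctly sized test. It is a modest but essentially free improvement, not a threat to the validity of the trial.

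**What to change.** In the Plan of analysis, state that IL-8 and the other continuous outcomes will be compared in models containing allocated arm, the baseline value where available, study site and procedure type, with the last two as fixed effects. Align the adjustment named in the Primary outcome section. If a SAP already does this, a cross-reference is enough.

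The cost is wording and about 5 degrees of freedom out of 150 to 170 patients; no extra patients, visits or samples are needed. As optional clarification, the same edit could fix the IL-8 scale in advance and say that the five postoperative times enter one combined repeated-measures comparison.

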#### Sensitivity analyses

Sensitivity analyses will include (1) per-protocol analyses and safety analyses will consider the likely effects of patient withdrawals and protocol non-compliance on the trial results; (2) consider the interaction between the intervention and the age of blood transfused, that is, those who receive only blood less than 14 days old versus those that receive any blood over 14 days old, on the basis that the proposed intervention is expected to prevent the risks attributed to prolonged blood storage.

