#### Red cells

Allogenic RBC, harvested in citrate-adenine-phosphate-dextrose, buffy coat removed, leucocyte depleted, saline-adenine-glucose-mannitol stored red cell units, supplied by National Health Service Blood and Transplant as per standard practice will be used. For the intervention, each unit of RBC will be added to a continuous autotransfusion system (CATS, Fresenius AG, Bad Homburg, Germany), washed using a centrifugal method, as per the device instructions. The washed RBC will then be immediately administered to the patient as per standard practice. Washing may be impractical in bleeding patients where there is cardiovascular instability, and clinician discretion may lead to the administration of unwashed cells in the washed group in breach of protocol. The clinical indication and timing of every transfusion, and whether or not washing has occurred as indicated will be recorded. The haematocrit (Hct) threshold for transfusion will be 23. Clinician discretion may also allow variation in this threshold in certain situations, that is, bleeding, where Hct thresholds are impractical.

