#### Deviations from protocol

In the event of any deviation from the trial protocol, defined as the administration of a washed unit to a patient randomised to the unwashed arm or vice versa, the deviation will be documented and the patient will continue to be treated according to the randomised allocation for all subsequent transfusions.

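### A per-protocol analysis that excludes washed-arm patients given unwashed units would probably favour washing; a complier-average effect should be the main non-compliance analysis

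*Protocol article*

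**What the plan says.** All references are to the protocol article.

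- **Sensitivity analyses:** the first item is that "per-protocol analyses and safety analyses will consider the likely effects of patient withdrawals and protocol non-compliance on the trial results". The per-protocol population is not defined in the article.
- **Red cells:** "Washing may be impractical in bleeding patients where there is cardiovascular instability, and clinician discretion may lead to the administration of unwashed cells". The sentence goes on to place this in the washed group and to call it a breach of protocol. Whether washing took place is recorded for every transfusion.
- **Deviations from protocol:** a deviation is "defined as the administration of a washed unit to a patient randomised to the unwashed arm or vice versa". The patient then returns to the allocated treatment for later transfusions, so compliance can be partial.
- **Measures taken to avoid bias** and **Plan of analysis:** the trial is analysed by intention to treat.
- **Table 1:** compliance with the washing protocol is a listed secondary outcome.
- **Duration of treatment in the trial:** the intervention runs from the start of surgery to 48 h.

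**The concern.** The definition of a deviation is symmetric, but the behaviour the protocol expects is not. An unstable bleeding patient in the washed arm may be given unwashed cells and so deviate. The same patient in the control arm is given unwashed cells and complies. The article gives no matching reason for washing a control patient's blood.

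The patients concerned are likely to have a worse prognosis on the article's own account. The Primary outcome section links transfusion to raised IL-8, and the Introduction links severe blood loss to more death and organ injury. If they are removed from one arm while their counterparts stay in the other, randomisation no longer protects the comparison.

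What is at stake is interpretation. A diluted or null intention-to-treat result beside a favourable per-protocol result invites the reading that washing works when it is actually given. Part of that contrast could be selection, and an analysis with a predictable lean cannot serve as a check of robustness to non-compliance.

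**Working it through.** **The plan's own figures.** The article gives no compliance rate and no per-protocol figure to reproduce. Its yardstick is the target difference of 0.4 SD, with a "moderate correlation of 0.7 between preintervention and postintervention measures and between repeated postintervention measures", on the basis that "there will be one baseline and five postoperative measures", and "we estimate that a sample size of 150 patients" (75 per arm). With the mean of five measures and no baseline adjustment, the variance factor is (1 + 4 × 0.7)/5 = 0.76. Then n per arm = 2 × (1.960 + 0.842)² × 0.76/0.4² = 74.6, so 75 per arm or 150 in total, at 80% power. At the 90% stated in Statistical analyses the same formula gives 100 per arm. The abstract states 80%. That discrepancy is a separate matter; here I need only 75 per arm and two variance factors: 0.76 (post-operative mean) and 0.76 − 0.7² = 0.27 (post-operative mean adjusted for baseline).

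**Formula for the bias.** Suppose there is no true effect. Let a share f of the washed arm be excluded, with mean IL-8 d SD above the rest of that arm (mean m).

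- Whole washed arm = control arm = m + f × d.
- Per-protocol washed arm = m.
- Per-protocol difference = m − (m + f × d) = −f × d, in favour of washing.

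**Size.** Both f and d are assumptions.

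| f | d = 0.25 | d = 0.5 | d = 1.0 |
|---|---|---|---|
| 5% | 0.0125 | 0.025 | 0.05 |
| 10% | 0.025 | 0.05 | 0.10 |
| 20% | 0.05 | 0.10 | 0.20 |
| 30% | 0.075 | 0.15 | 0.30 |

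Against the 0.4 SD target, 0.0125 is 3%, 0.10 is 25% and 0.30 is 75%.

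**Chance of a falsely favourable per-protocol test (nominal 2.5%).** Take f = 20%, d = 0.5 and 75 per arm before exclusion.

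- Factor 0.76: SE = √0.76 × √(1/75 + 1/60) = 0.151. The shift is 0.10/0.151 = 0.66, and Φ(0.66 − 1.96) = 9.7%.
- Factor 0.27: SE = √0.27 × √(1/75 + 1/60) = 0.090. The shift is 1.11, and Φ(1.11 − 1.96) = 19.8%. Here d means the excess that remains after baseline adjustment.

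Over the whole table the chance runs from about 3% to 48% (factor 0.76) or 89% (factor 0.27).

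**With a true effect of −0.40 in those washed.** Take d = 0.5 and no washing at all in the excluded patients. Then intention to treat = −0.40 × (1 − f), per-protocol = −0.40 − f × d, and complier estimate = intention to treat/(1 − f).

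| f | Intention to treat | Per-protocol | Complier |
|---|---|---|---|
| 10% | −0.36 | −0.45 | −0.40 |
| 20% | −0.32 | −0.50 | −0.40 |
| 30% | −0.28 | −0.55 | −0.40 |

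A simulation of 2 million patients per scenario agreed to within about 0.005. With no true effect it put the complier estimate at about zero.

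**Partial compliance.** Suppose the non-compliers still gain half the effect because some of their units were washed. Intention to treat is then −0.40 × (1 − f/2) = −0.38, −0.36 and −0.34.

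- If only fully washed patients count as exposed, the complier estimate is −0.38/0.9 = −0.42, −0.36/0.8 = −0.45 and −0.34/0.7 = −0.49, which overstates.
- If anyone with at least one washed unit counts as exposed, these patients stay in the exposed group and that overstatement does not arise. The estimate is then the effect of washing as delivered.

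**Who is excluded under a per-unit rule.** If excluding deviators meant any single wrong unit, then at an assumed 5% miss rate per unit the chance of exclusion is 1 − 0.95² = 10% with 2 units and 1 − 0.95¹⁰ = 40% with 10. Such a rule would fall hardest on the large-volume recipients for whom the trial selects.

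**The case against.** The strongest reply is that the article defines no per-protocol set. The section on deviations governs documentation and later treatment; it does not say that deviators leave the analysis. The definition covers both arms, and the sensitivity analysis also names withdrawals, which can occur in either. A statistical analysis plan may define the set differently. This stands: a reader might infer that the plan drops the sickest patients from the washed arm only, but the article does not say so. What remains is conditional. A set that excludes the deviators whom the article itself predicts would have this lean.

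Second, per-protocol is only a sensitivity analysis and compliance is reported, so readers could see how many patients deviated. That limits the damage but does not make the analysis a sound test of robustness.

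Third, a reader might infer that safety events would be hidden. The article does not support this. It names per-protocol and safety analyses side by side without saying that safety uses the per-protocol set, and it plans to tabulate adverse outcomes.

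Fourth, the complier estimate has limits. With one binary instrument its test is essentially the intention-to-treat test rescaled, so it adds no power. Counting one washed unit as exposure averages over full and partial washing. Patients never transfused and patients whose washing was skipped are both unexposed, although only the latter are non-compliant. The method also assumes that allocation acts on IL-8 only through washed units, and clinical staff are not blinded. These points argue for adding the estimate with its assumptions stated, not for presenting it as free of assumptions.

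**Conclusion.** The point holds in conditional form. If the per-protocol set excludes washed-arm patients who received an unwashed unit, it would probably favour washing, because the article expects such patients to be the unstable bleeders and expects them in that arm.

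The size is unknown. It is f × d, and neither value is in the documents. At an assumed 5% it is negligible to small; at an assumed 20% or more with d of at least 0.5 it reaches a quarter of the target difference or more. The direction rests on the excluded patients having higher IL-8 than the rest of their arm, which the article's statements on transfusion make likely but do not prove.

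A reader might go further and conclude that the trial's main result is biased. It is not: the primary analysis is by intention to treat and does not depend on this choice. This is an inexpensive improvement to a secondary analysis.

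**What to change.** Make the main non-compliance sensitivity analysis a complier-average causal effect on IL-8:

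- randomised arm as instrument, in a two-stage regression;
- exposure = at least one washed allogenic unit by 48 h, with patients never transfused counted as unexposed in both arms;
- all randomised patients kept in their allocated arm;
- the same outcome scale as the primary analysis, with baseline IL-8, centre and procedure type as covariates in both stages.

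Optionally repeat it with the proportion of allogenic red cell units washed as exposure (zero for patients never transfused), because compliance can be partial.

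If a per-protocol analysis is kept, define its population, label it descriptive, report the exclusions and their reasons by arm, and state that it probably favours washing.

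**Cost:** wording and one standard model. No new data are needed, since washing is recorded for every transfusion. The interval is wider by a factor of 1/(1 − f): at f = 20%, the SE rises from √0.76 × √(2/75) = 0.142 to 0.178, or from √0.27 × √(2/75) = 0.085 to 0.106 with baseline adjustment. Patients never transfused would widen it further, because they reduce the difference in exposure between arms. There is no gain in power over the intention-to-treat test.
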